### 7.2 Recruitment and screening

The therapy management office will notify the PL when patients matching the inclusion criteria are referred to the outpatient department of the study site. The time lapse between referral and first treatment appointment is approximately 2 weeks. During this time the PL will contact the patient to inform about the study and invite him or her for a baseline assessment. Additionally, local care providers and physicians will be contacted and information leaflets provided to the public (online media, print media, local health institutes and Spa-Centres). These flyers will not be distributed before ethical approval for their content is given. Interested participants will contact the PL to receive detailed information (as described above). If the patient was not referred to study site by an external physician, they must first be examined by the clinic's internal rheumatologist to confirm diagnosis of chronic lumbosacral spinal pain (including radicular pain).

Healthy participants will be invited through homepage advertisement, local media, and internal pin-board (for staff members).

### 7.3 Assignment to study groups

A technical assistant, otherwise not involved in the study, will compute the blocked randomisation sequence. The sequentially numbered list will be kept out of reach from the PL. Allocation remains concealed to the outcome assessor (see Figure 1 and Table 1).

## **7.4 Criteria for withdrawal / discontinuation of participants**

The measurement event or intervention will be immediately terminated if any one of the following events occurs:

- Participant refuses to give or withdraws written consent.
- Participant decides to end measurements or intervention for any given reason.
- Project leader or therapist notices uneasiness of the participant during assessments or during experimental intervention (e.g. dizziness or unexpected increase of pain level).
- Sustained increase of symptoms after training sessions after the first 9 sessions.
- Participant is injured after fall or other trauma (e.g. fracture).

## 8. STUDY INTERVENTION

### 8.1 Identity of Investigational Products (treatment / medical device)

#### 8.1.1 Experimental Intervention

The experimental group will receive added PPT to the conventional physiotherapy. PPT will be applied by means of a neuro-orthopaedic medical device (Posturomed®, see section 3.2). The Posturomed allows adaptive oscillation in the horizontal plane. Therapy instructions advise seven stages of difficulty. In all stages the patient is asked to provoke oscillation by stepping on site. After three steps, the patient must stand still on one leg for 2 seconds before he or she repeats the steps. Difficulty is increased by a) decreasing the damping through release of the breaks and b) through added juggling of a ball during the motor task (dual-task and divided attention). The next stage is reached once stabilisation in the previous stage is secured.

[figure not shown]

#### 8.1.2 Control Intervention

Added to conventional therapy, as administered to all participants, the control group will receive added LIT. The control intervention will consist of 10 minutes of low intensity endurance training (Borg scale 6-9). The patient will be instructed in treadmill, stationary cycling or cross-trainer functions. The speed should be adjusted to the level where the patient would still be able to talk comfortably.

[figure not shown]

#### 8.1.3 Packaging, Labelling and Supply (re-supply)

Not applicable.

#### 8.1.4 Storage Conditions

Devices are re-usable and do not require any specific storage regulation.

### 8.2 Administration of experimental and control interventions

#### 8.2.1 Conventional Therapy (both groups)

All participating patients will attend usual care according to their treatment plan (taking part in the study does not affect the treatment plan). A physiotherapy referral requests 9 treatments, each of which takes 30 minutes. These will take place twice a week for 4.5 weeks. The study protocol does not dictate the content of the physiotherapy sessions themselves, but detailed documentation of provided treatments is required (therapy documentation sheet). Additionally, the aim of the

physiotherapy sessions should always include reduction of muscular imbalances and optimisation of posture.

### **8.2.2 Experimental Intervention**

The exercise intervention under investigation is performed with a non-invasive therapy product. The patient stands on a platform with minimal sway and tries to stabilise upright posture on one leg. The aim of each exercise is to train inter-spinal muscles and improve sensorimotor control of postural muscles. The training is applied one to two times per week after the patient's regular visit to physiotherapy. The patient is then instructed in the usage of the device by a therapist who is trained in proprioceptive training methods. The exercise is executed in 5 sets of 1.5 minutes with a 30 to 60 seconds break in-between each set. In order to provoke any training effects, the difficulty of the exercise must be adapted to the individual's skills and abilities. A therapist will be nearby to instruct each stage of difficulty and to promote the patient to the next higher stage once the previous one is mastered adequately. The criteria are defined in the instruction booklet [8].

### **8.2.3 Control Intervention**

The low intensity cardiovascular exercises will be performed a cardio-device of choice. The patients will be instructed to walk (not run) or cycle at a comfortable pace with low intensity for ten minutes. Initial settings and a general introduction will be given by the therapist. Once individual comfort zone (speed, at which participant feels comfortable to walk and talk for 10 minutes) is set, the intensity is not changed.

## **8.3 Dose / Device modifications**

Frequency and dose remain constant over the entire trial. Difficulty levels of the experimental intervention may be adapted as described above.

## **8.4 Compliance with study intervention**

Generally, the patients must conduct the training themselves. A medical fitness instructor will be nearby to oversee the training and will be instructed to record any deviation from the prescribed exercise regimen. The patient will also be asked to record deviations from training regimen on his or her exercise diary. Home exercises will not be controlled for compliance but noted on the diary.

## **8.5 Data Collection and Follow-up for withdrawn participants**

Withdrawn patients will be invited to take part at the assessments only. If refused, intention-to-treat analysis will be applied with carry-forward data.

## **8.6 Trial specific preventive measures**

Not applicable.

## **8.7 Concomitant Interventions (treatments)**

Co-interventions cannot be controlled in the clinical setting of rehabilitation.

## **8.8 Study Drug / Medical Device Accountability**

Not applicable.

## **8.9 Return or Destruction of Study Drug / Medical Device**

Not applicable.

## 9. STUDY ASSESSMENTS

Table 2: Study procedure chart

[figure not shown]

Table 3: Study procedures at each visit:

|                                          |                                                                                                                                                                                                                                                                                                                                                                                                                                                                                          |
|------------------------------------------|------------------------------------------------------------------------------------------------------------------------------------------------------------------------------------------------------------------------------------------------------------------------------------------------------------------------------------------------------------------------------------------------------------------------------------------------------------------------------------------|
| 1st contact: Inform & Invite             | If the willingness to partake is confirmed (within 1-2 days), an appointment for eligibility evaluation and baseline assessment is made.                                                                                                                                                                                                                                                                                                                                                 |
| 1st visit
Eligibility & Baseline      | 
4 to 7 days prior to the 2nd visit, a baseline assessment shall confirm eligibility and pre-test data is recorded.
 
 
• Eligibility criteria assessed (incl. medical examination)
 
• Pain & Function assessed with validated questionnaires
 
• Cervical proprioception recorded as cervical joint repositioning sense
 
• Postural control assessed with 2D-motion tracking and UCM analysis
 
 |
| 2nd visit
Pre-intervention assessment | 
On the day of the first treatment the pre-intervention assessment is recorded.
 
 
• Pain & Function assessed with validated questionnaires
 
• Postural control assessed with 2D-motion tracking and UCM analysis
 
• Cervical proprioception recorded as cervical joint repositioning sense
 
                                                                                                                     |
| Randomisation                            | The patient is allocated to either the experimental or the control group.                                                                                                                                                                                                                                                                                                                                                                                                                |
| 3rd to 12th visit
9 PT treatments     | The patient visits the clinic as he or she would have done for normal physiotherapy treatment. Added to the 30 minutes of physiotherapy, the patient attends additional 15 minutes of either PPT or TrT.                                                                                                                                                                                                                                                                                 |
| 13th visit
Intermediate assessment    | 
1 to 2 days after last treatment, the patient will undergo an intermediate effect assessment.
 
 
• Pain & Function assessed with validated questionnaires
 
• Cervical proprioception recorded as cervical joint repositioning sense
 
• Postural control assessed with 2D-motion tracking and UCM analysis
 
                                                                                                      |

| 4 week interruption    |                                                                                                                                                                                                                                                                                                                                                                                   |
|------------------------|-----------------------------------------------------------------------------------------------------------------------------------------------------------------------------------------------------------------------------------------------------------------------------------------------------------------------------------------------------------------------------------|
| 14 th visit | 
1 to 2 days after treatment, the patient will undergo post-intervention effects assessment.
 
 
• Pain & Function assessed with validated questionnaires
 
• Cervical proprioception recorded as cervical joint repositioning sense
 
• Postural control assessed with 2D-motion tracking and UCM analysis
 
 |

## 9.1 Experimental procedure

Measurements will take place within the clinic's facilities (Reha Rheinfelden) featuring all necessary instruments to record data, including the Posturomed® to induce instability, the Haider Bioswing accelerometer to record plate deflection, a Zebris force sensor plate to record centre of pressure (COP), high-speed cameras for motion tracking and the motion analysis system (software and computer).

## 9.2 Assessments of outcomes

### 9.2.1 Assessment of primary outcome

Whilst preparing the setup and software configuration, the subject will be given 10 minutes time to fill in the personal data sheet, including the VAS scales for pain, and the ODI questionnaire for functional status. The questionnaires will be filled in by the patients at every measurement event (BL, T0, T1, and T2).

Self-reported impairment in daily activities will be assessed using the German version of the Oswestry Disability Index (ODI-D), which shows a good reliability. The ODI has ten sections about daily activities (pain, body hygiene, lifting objects, walking, sitting, standing, sleeping, sexual behaviour, social life, and travelling). Each section can be rated from 0 (no pain during activity or pain getting worse) to 5 (I cannot do it myself). The total score is in percentage of the total 50 points, if each section was answered (45, if 9 sections were answered, and so on). The end score will be from 0% (minimal impairment) to 100% (bedridden). A change of 4 points is considered as clinically relevant [26].

Self-reported pain will be assessed using the German version of the Visual Analogue Scale (VAS). It shows a good reliability with a correlation of 0.937 between the first and the second assessment. The VAS is a 100mm line with two endpoints representing the extreme states "no pain" and "pain as bad as it could be". A minimum of 13 mm difference on the scale is considered as clinical relevant [26].

### 9.2.2 Assessment of secondary outcomes

The secondary outcomes, joint repositioning sense and postural control, will be measured at each measurement event (BL, T0, T1, and T2).

The experimental set-up consists of the neuro-orthopaedic therapy system Posturomed® 202 with handrail (Haider Bioswing, Pullenreuth, Germany), an attached provocation module (Haider Bioswing GmbH, Pullenreuth, Germany), a high-speed camera Basler A602F (Basler AG, Ahrensburg, Germany), a personal computer with Windows 8 operating system to which the camera is attached with USB 3.0, an accelerometer attached to the base-plate of the Posturomed®, and optical markers to measure different joint deflections and joint motion. The markers will be tracked with the motion analysis software Templo (v.7.1.304, Contemplas GmbH, Kempten, Germany). COP is measured by means of a Zebris FDM-S force measuring plate on top of the swaying platform.

After evaluating primary outcomes, the participants will be equipped with markers as shown in Figure 2 below. After familiarisation with the Posturomed's labile surface, he or she will be instructed to adopt an upright posture with the arms folded across the chest (in order to keep hip markers visible). On the cue "ready-steady-go", the assessor will release the platform from its 5 cm deflection. The swaying is recorded until complete damping of the oscillation has occurred (approximately 15

seconds). As participants will be standing on both feet, any facilitation of the task through engaging brakes would make the task too easy (as tested in pre-pilot tests). Hence, all of the device's brakes will be released for this test allowing maximal sway. The camera setup will record the entire task. The task will be repeated five times for each patient. The arithmetic mean of the five trials will be used for further analysis.

Optical markers in combination with a high-speed camera are used in the study for motion tracking of joint configurations. The reflecting markers, eleven in total, are placed on the participants as depicted in Figure 2 below: At the corner of the eye, the mastoid process, shoulder (acromion), hip (greater trochanter), knee (lateral femoral condyle), ankle (lateral malleolus), toe, heel and the platform surface. There are additionally two markers on the iliacus superior for calculation of the pelvic tilt angle and one on the floor for calibration purposes. The marker configuration is based on recommendations from Scholz et al. [27]. The markers are 16mm in diameter and will be attached using skin-friendly adhesive tape.

Two cameras will track these reflecting markers with a spatial resolution of 1.5 megapixels and a temporal resolution of 60 frames per second, which has shown to be enough for the purposes (tested in pre-pilot studies). Calibrations will be carried out at the beginning of the performance of the task.

[figure not shown]

**Figure 2: Marker configuration for video-based postural control assessment**

An additional setup is installed to measure cervical proprioception (Figure 3). On a wall facing a chair, there are vertical lines that represent the 30° and 60° angle to the left and the right side. Participants are blindfolded to avoid opening of the eyes and visual input during testing. Additionally, they wear a headgear to prevent acoustical input like computer ventilation (instructions are still perceptible). A laser pointer is fixed on the headgear. A computer mouse fixed to the hand side of the participant can be clicked to indicate when the head position is perceived to be at the instructed angle. Each click records the exact time and allows post-measurement synchronisation with the motion-tracking data. Cameras stand both lateral and posterior to the participant. The lateral camera records any possible deviations in posture of the trunk during measurements.

The testing order is randomized. The instructor gives cues following the test protocol. Five trials are used because more than three repetitions seem to be needed in order to reduce variability of the results but less than ten to avoid fatigue and noncompliance of Participants. Participants hold the laser pointer on the target angle line for 15 s (with one click on the left mouse-button for data of reference position). After returning to neutral position, participants replicate the target angle position followed by a mouse-click to confirm position. This procedure is repeated five times for one target angle before proceeding to the next angle. To measure repositioning of neutral position, participants hold in their personal, most natural way of NP and click the mouse. After holding NP for 15s, they perform a full right and left rotation of the head, directly return to NP and click the mouse.

[figure not shown]

**Figure 3: Measurement set-up for cervical proprioception (head-repositioning error).**

The setup was pilot-tested in order to define optimal settings for the recording (e.g. light, camera distance, marker-repositioning).

The information on change of angular configuration during the task will be used to apply the uncontrolled manifold approach (UCM). The UCM hypothesis states that the central nervous system (CNS) does not eliminate redundant degrees of freedom. It uses these degrees of freedom to ensure stable performance of motor tasks. A UCM spans a subspace consisting of all joint angles which ensure a stable movement and do not affect the controlled variable. Joint angle combinations which lie in a subspace orthogonal to the UCM lead to a deviation from this stable condition and therefore affect the controlled variable. The mathematical method is described in detail by Scholz et al. [20].

Additionally the joint repositioning error will be analysed from this data. The joint repositioning error is the deflection of a joint or joint angle after a movement in comparison to the joint configuration before the movement. The three-point angle on all recorded segments will be analysed. This error can be a measure for conscious body position perception [28].

There is a pressure sensor (Zebris FDM-S) and an accelerometer with a sampling frequency of 1000Hz on the base-plate, which will be used for calculation of the centre of pressure and the sway of the platform, respectively. These parameters provide further information about postural control.

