| Background and Rationale:                       | Sensorimotor training (SMT) is popularly applied as preventive or rehabilitative exercise method in various sports and rehabilitation settings, especially when postural control, linked to proprioception, is suspected to be deficient. Its effect, however, on pain and function is only poorly evaluated.                                                                                                                                                                                                                                                                               |
| Objective(s):                                   | The projects has two main objectives:

 
1. Measure effects of a four- to five- week sensorimotor training intervention, compared to low intensity endurance training, on musculoskeletal pain, functional status, postural control, and proprioception in patients with chronic non-specific low back pain.
 
2. Evaluate the relationship between cervical proprioception, postural control, and chronic non-specific low back pain (CNLBP) compared to healthy controls.
 
                                                        |
| Outcome(s):                                     | Primary outcomes:
Pain & Functional status: Visual Analogue Scale (VAS) and Oswestry Disability Index (ODI)

Secondary outcomes:
Postural Control: Sway of base of support (BOS), centre of pressure of BOS, Centre of Mass, Angular variation of involved segments, Uncontrolled Manifold Index before and after 5-week intervention.

Proprioception: Joint Repositioning Error of cervical, lumbar, hip, knee and ankle joints (before versus after perturbation) and head repositioning sense (HRS) before and after 5-week intervention. |

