## **11.4 Planned Analyses**

Baseline imbalance between groups will be tested with a student t-test. Differences in means between healthy participants and patients with CNLBP will be analysed with independent student t-tests. A mixed (2) Group x (2) ME ANOVA with repeated measures during ME will be conducted for each dependent variable individually (Pain VAS, Functional Status ODI, Postural Control COM and CM, Proprioception JRE, and Motor Equivalence UCM).

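### The joint-angle change across the platform perturbation is classed as proprioception, although that task asks nobody to reproduce a joint position, and section 11.4 may test it under that label

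*Protocol*

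**What the plan says.** The protocol describes two position errors.

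- **Perturbation error.** The synopsis lists, under proprioception, "Joint Repositioning Error of cervical, lumbar, hip, knee and ankle joints (before versus after perturbation"; head repositioning sense follows as a separate item. Section 9.2.2 derives the error from the angular data of the platform-release task that also feed the uncontrolled manifold (UCM) analysis: "Additionally the joint repositioning error will be analysed from this data". It defines it thus: "The joint repositioning error is the deflection of a joint or joint angle after a movement in comparison to the joint configuration before the movement". It then states: "This error can be a measure for conscious body position perception".
- **Head-repositioning error.** Section 9.2.2 describes a separate blindfolded test in which the participant holds a target head angle, returns to neutral, reproduces the target and confirms with a mouse click.

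For the platform task, 9.2.2 has the participant "instructed to adopt an upright posture with the arms folded across the chest". The assessor then releases the deflected platform and the sway is recorded until it dies out. Section 4.3 gives the goal as regaining normal stance.

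Section 5.2 names only the head-repositioning error as the proprioceptive endpoint. Section 4.3 and the third hypothesis in 11.1 likewise speak only of cervical proprioception. Section 11.4 lists "Proprioception JRE" as the single proprioception variable, beside a separate UCM variable.

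**The concern.** A repositioning error measures position sense only if the participant has a reference position and is trying to return to it. Without that instruction, a changed joint angle after the sway may simply be another acceptable way of standing. The UCM account in 9.2.2 says as much of redundant joint freedom: "It uses these degrees of freedom to ensure stable performance of motor tasks".

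If the perturbation error is analysed as proprioception, a between-group difference in how people settle after a disturbance could be published as an effect of training on position sense. Two of the three research questions in section 4 concern cervical proprioception, so the label affects what the trial may conclude. The term in 11.4 also leaves open which of the two errors is tested. If it is the perturbation error, the endpoint named in 5.2 has no place in the listed group-by-time analyses.

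**Working it through.** **1. Does the platform task contain the elements of a position-sense test?** Both columns come from 9.2.2, with the goal of the platform task from 4.3.

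| Element | Head test | Platform release |
|---|---|---|
| Reference | Held target angle or own neutral position | Whatever posture precedes release |
| Instruction | Reproduce it | Stand upright, regain stance |
| Vision | Blindfolded | No restriction described |
| Response | Click when position is felt to be reached | None; sway is recorded |
| Error | Deviation from the reference | Angle after against angle before |

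The platform task has no joint-angle target, no reproduction step and no confirming response. Regaining stance is a general postural goal that many joint configurations satisfy.

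**2. Which error does 11.4 test?** The synopsis uses the term joint repositioning error for the perturbation measure and a different term for the head test, which points to the perturbation error. Sections 4.3, 5.2 and 11.1 point to the head test, and Table 3 calls the latter cervical joint repositioning sense. The word cervical does not settle it, because the synopsis includes the cervical joint in the perturbation error too. The text allows either reading, or both.

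**3. Could the perturbation error conflict with the UCM outcome?** There is no stated figure to reproduce. A linear model shows what is possible. The following inputs are assumptions, not protocol values:

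- five joints (the synopsis names five regions) and a one-dimensional controlled variable, giving four within-manifold dimensions and one orthogonal dimension;
- variances per dimension Vu (within the manifold) and Vo (orthogonal), in arbitrary units;
- before-after correlations ru and ro, with ro = 0 throughout;
- index = (Vu − Vo) / [(4Vu + Vo)/5], since the protocol gives no formula.

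The root-mean-square error per joint is √{2[4Vu(1 − ru) + Vo(1 − ro)]/5}. For Vu = Vo = 1 and ru = 0 it is √(2 × 5/5) = 1.41. For Vu = 4 it is √(2 × 17/5) = 2.61, and the index is 3/3.4 = 0.88. The return error along the controlled direction, √[2Vo(1 − ro)], is 1.41 in both cases.

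| Change | Index | Joint error |
|---|---|---|
| Vu 1 to 4, ru = 0 | 0 to 0.88 | 1.41 to 2.61 |
| Vu 1 to 4, ru = 0.5 | 0 to 0.88 | 1.10 to 1.90 |
| Vu 1 to 4, ru = 0.9 | 0 to 0.88 | 0.75 to 1.02 |
| Vu 1 to 4, ru = 1 | 0 to 0.88 | 0.63, unchanged |
| Vo 1 to 0.25, Vu = 1, ru = 0 | 0 to 0.88 | 1.41 to 1.30 |
| Vu 1 to 4 while ru goes 0 to 0.75 | 0 to 0.88 | 1.41, unchanged |
| Vu 1 to 4 while ru goes 0 to 0.9 | 0 to 0.88 | 1.41 to 1.02 |

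The same rise in the index can thus go with a larger, equal or smaller joint error. A signed mean error stays near zero in every case, although its spread changes. Simulation with 200,000 draws agreed with the formula.

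**The case against.** The wording in 9.2.2 is hedged, since it says the error can be such a measure, and it cites a source that cannot be checked here. The limitations in 6.1 already admit that proprioception is measured indirectly. Participants are asked to regain stance, which is more than merely standing. The body of the protocol largely treats head repositioning as the proprioceptive endpoint, so 11.4 may intend that test. All of this is fair and limits the point. It does not remove it: the caveat in 6.1 takes for granted that the error is a conscious one, which is the matter in doubt, and the synopsis and 9.2.2 still classify the perturbation error as proprioception.

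A reader might infer more: that the error must rise with the joint flexibility the UCM index rewards, so that the two outcomes oppose each other by construction and stiffer patients would score as having better proprioception. The documents do not support this. As the table shows, the rise needs an absolute or squared error, with orthogonal variance and before-after correlation held fixed and the within-manifold correlation below 1. The protocol does not say whether the error is signed or absolute, and gives the UCM index neither a formula nor a scoring direction. Its patient-versus-healthy hypothesis on variability in 11.1 is non-directional, and the corresponding null refers to optimal variability. Section 3.1 does treat lack of variability as harmful, but that is rationale, not a scoring rule.

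**Conclusion.** The point holds as a fault of measurement and labelling. A before-after posture difference, from a task without a reproduction instruction, is classed as proprioception, and 11.4 may test it as such in place of the head-repositioning error that 5.2 names. This rests on the text alone and needs no model.

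The possible conflict with the UCM outcome is secondary and conditional. It matters because the first alternative hypothesis in 11.1 expects the experimental group to improve more on all outcomes, so under the stated conditions one change could count as a gain on one variable and a loss on another. Its size in this trial cannot be derived from the protocol; the model figures are illustrative.

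The scope is modest: secondary outcomes in a trial that calls itself pilot and exploratory. Pain, disability, sample size and the head test itself are unaffected. It is still worth correcting, because it changes what the trial can conclude about proprioception.

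**What to change.** - In the synopsis, 9.2.2 and 11.4, name the head-repositioning error from the blindfolded target test as the proprioception variable, in line with 5.2.
- Reclassify the joint-angle difference across the perturbation as a descriptive postural-control measure, and state whether it is signed or absolute.
- Delete the sentence in 9.2.2 that it can measure conscious position sense.

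Reporting the difference only as separate within-manifold and orthogonal parts is not required; that is an analytic preference. The cost is a change of wording and one fewer proprioception variable. Both data sets are already planned, so no new data are needed, and neither sample size nor alpha changes.
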